### Informed consent process

The first author will explain the research objectives and method to pregnant women meeting the inclusion criteria at the time of their admission to the labor and birth ward. The first author will then obtain written consent from patients willing to participate in the trial.

### Sample size estimation

To calculate the minimal clinically important difference (MCID) for the duration of the first stage of labor and the pain score, we used previous study data which examined the effect of auricular [24] and body [25] acupressure on labor pain intensity and labor duration. Using the method of Wyrwich et al. [26], MCID score for significant pain reduction during labor was one score based on visual analogue scale. Using the G*Power software 3.1.9.2, α = 0.05, and power = 0.80, considering SD = 1.4 and M0 = 7.2 for the labor pain score and 10% drop out of subjects, the sample size was calculated to be 30 patients for each group.

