Auriculotherapy (AT; also known as auricular therapy) is a branch of acupressure spreading throughout the world. AT is based on a long-standing tradition and was modified and updated by [name]. Also, the World Health Organization considers AT a form of microacupuncture that can affect the whole body [16]. AT comprises several types of therapy, including auricular acupuncture, electro-stimulation, and acupressure. Various studies have reported promising results when using AT for the control of pain caused by backache, [17] pelvic fractures, [18] dysmenorrhea, [19–21] and polycystic ovarian syndrome [22]. However, only a limited number of studies have been done on the effect of auriculotherapy on labor pain, and these have yielded inconsistent results. Accordingly, in Rastegarzadeh et al.’s work, auriculotherapy led to a significant reduction in labor pain among nulliparous women [23], whereas a study by Maftoni and Shimo indicated that use of auriculotherapy caused no significant reduction in the studied women’s labor pain [24].

As can be inferred from investigations, most of the studies on body acupressure have more frequently applied pressure on one or two points; only a few studies have focused on a combination of points affecting the pain and progress of labor. Furthermore, some studies have been conducted on the effect of auricular acupressure on the reduction of different pain throughout the body, the results of which have confirmed the effectiveness of this technique. However, only a few studies have addressed the effect of auricular acupressure on labor pain, yielding inconsistent results [3, 4]. Given the small number of studies on the effect of body acupressure at multiple points and auricular acupressure on the pain and duration of labor, we designed the present study. In this clinical trial, the primary objective is to compare the effects of auricular acupressure, body acupressure, and routine treatment on the pain score at the time of 4-cm and 10-cm cervical dilations. The secondary objective is to investigate the effects of the described interventions on the duration of the first stage of labor, which is defined as the time interval between the 4 cm and 10 cm cervical dilations. This is a single-center, parallel, double blinded randomized controlled trial to investigate the superiority of auricular acupressure and body acupressure compared with routine care during the first stage of labor. The allocation ratio for the groups is 1:1:1.

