### Data analysis

Once collected, the data are imported into SPSS-16 software. Firstly, normality of the data distribution will be investigated (via three methods, including Kolmogorov–Smirnov, histogram, and dispersion and central indices) and if the distribution of variables is not normal, then we will use an appropriate transformation. To compare the labor duration and pain score among the research groups, one way ANOVA test will be used, which will be followed, in case of significance, by Scheffe post hoc test. If there are potential confounding variables, a multiple linear regression test will be used. We will check for the assumptions and concerns of the regression model. Furthermore, Chi-squared test will be used to compare the categorized demographic variables in the studied groups. In order to compare the quantitative variables, in case of normal and abnormal distribution of the variables, ANOVA and Kruskal–Wallis tests will be used, respectively. The post hoc of these tests will be reported if needed. The study will be analyzed using an intention-to-treat (ITT) approach and using a multiple imputation strategy to account for missing outcomes in ITT. Also, apropos of the significance level, 0.05 is considered significant.

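### Thirty women per group including 10% dropout does not give 80% power for a 1-point difference under the planned three-group ANOVA, and gives clearly less per Scheffe contrast

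*Protocol article*

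**What the plan says.** The Sample size estimation section sets the target difference: "MCID score for significant pain reduction during labor was one score based on visual analogue scale". It gives the error rates ("Using the G*Power software 3.1.9.2, α = 0.05, and power = 0.80") and the variability ("considering SD = 1.4 and M0 = 7.2 for the labor pain score"), and ends with "10% drop out of subjects, the sample size was calculated to be 30 patients for each group". It does not name the test entered in the software, the sidedness, or how the three group means are assumed to lie.

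The Background states the aim, "to investigate the superiority of auricular acupressure and body acupressure compared with routine care", and the allocation: "The allocation ratio for the groups is 1:1:1".

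The Data analysis section says how labor duration and pain score will be compared among the three groups: "one way ANOVA test will be used, which will be followed, in case of significance, by Scheffe post hoc test". On the error rate it says "apropos of the significance level, 0.05 is considered significant", again without sidedness.

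**The concern.** A sample size statement should describe the power of the analysis that will be run. Here the calculation names no test, while the Data analysis section names a three-group F test and a post hoc procedure, both non-directional. If 30 per group does not deliver 80% under that analysis, the article promises more than the trial can give.

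The gap matters most at the post hoc step. The aim is superiority of each acupressure method over routine care, and those two conclusions come from pairwise contrasts, not from the omnibus F. If readers believe there was 80% power to detect 1 point, they may read a non-significant contrast for one arm as showing that no worthwhile benefit exists. The trial would have had only moderate power to find one.

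**Working it through.** **Inputs from the article.** Difference Δ = 1, SD σ = 1.4, alpha 0.05, target power 0.80, dropout 10%, three equal groups, 30 recruited per group. Evaluable per group: 30 × 0.9 = 27, or 81 in total. Standardised difference d = 1/1.4 = 0.714.

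**Assumptions of this check.** Common SD of 1.4 in all groups, and normal outcomes. The pattern of the three means is not stated, so two are shown.

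**Can 30 be reproduced?** Recruited n is evaluable n divided by 0.9, rounded up. The F and t results use the noncentral distributions. The rank-test results divide the t-test n by an efficiency of 0.955.

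| Calculation | Evaluable per group for 80% | Recruited per group |
|---|---|---|
| ANOVA, one group 1 point from the other two | 30 | 34 |
| ANOVA, means 0, 0.5, 1 | 39 | 44 |
| Two-sided t-test | 32 | 36 |
| Two-sided rank test | 34 | 38 |
| One-sided t-test | 25 | 28 |
| One-sided rank test | 27 | 30 |
| Three-group ANOVA with f set to d/2 = 0.357 | 27 | 30 |
| One given Scheffe contrast | 44 | 49 |

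Two rows reach 30 exactly, and neither is the planned analysis at a 1-point difference. The f = 0.357 row uses the two-group conversion. For three equal groups spanning at most 1 point, the largest SD of the means is √(2/9) = 0.471, so f cannot exceed 0.471/1.4 = 0.337.

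**ANOVA power at 27 per group.** The noncentrality is λ = n Σ(μᵢ − μ̄)²/σ², compared with F(0.95; 2, 78) = 3.114.
- One group 1 point apart: Σ = 2/3, λ = 27 × 0.667/1.96 = 9.18, power 0.763.
- Evenly spaced: Σ = 0.5, λ = 27 × 0.5/1.96 = 6.89, power 0.630.

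With no dropout (30 per group) these become 0.809 and 0.681. Under the favourable pattern, 30 is therefore the number needed before any allowance for loss.

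**Pairwise power at 27 per group.** The noncentrality is d√(n/2) = 0.714 × √13.5 = 2.624.
- Two-sided t-test, 52 df, critical value 2.007: power 0.731.
- One given Scheffe contrast, 78 df, critical value √(2 × 3.114) = 2.496: power 0.553 (0.610 at 30 per group).
- Both arms truly 1 point better than routine care (simulation): both Scheffe contrasts significant in about 39% of trials, at least one in about 71%.

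Requiring a significant F first costs nothing further, because a significant Scheffe contrast implies a significant F.

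**Difference detectable with 80% power at 27 per group.** About 1.04 points (ANOVA, favourable pattern), 1.09 (two-sided t-test), 1.21 between the extreme groups (ANOVA, evenly spaced) and 1.27 (one Scheffe contrast).

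**The case against.** The article states no sidedness and words its aim as superiority. A one-sided two-group rank test gives 27 and then exactly 30, and a one-sided t-test needs only 28 recruited and has 83% power at 27. A reader might infer that the stated inputs cannot give 30 at all, or that the two-group f was mistakenly put into a three-group ANOVA. The article supports neither reading: more than one route leads to 30, and it does not show which was taken. That part of the objection stands. It does not rescue the figure, because no section plans a one-sided test or a rank test for the pain comparison. Non-normal outcomes are to be transformed and then analysed by ANOVA, and neither the F test nor Scheffe is directional.

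A second objection is that the shortfall on the omnibus test is small: 76% against 80% under the favourable pattern, or 1.04 points detectable instead of 1.0. The uncertainty in an SD borrowed from earlier studies could easily exceed that. This is fair for that pattern, but not for evenly spaced means.

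Third, sizing a trial on the omnibus test is a legitimate choice, and the article does not claim 80% for each Scheffe contrast. That also stands, and a reader should not take 55% as the power of the whole design. It belongs to one given contrast; when both arms work, the figure runs from about 39% for both contrasts to about 71% for at least one. Even so, the superiority conclusions depend on those contrasts, so their power should be visible.

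Finally, regression is allowed if there are confounders. If the 4-cm score were used as a covariate, an assumed correlation of 0.3 with the 10-cm score would bring ANOVA power at 27 per group to about 80%, and 0.5 to about 88%. Both correlations are assumptions, and the adjustment is conditional in the plan, so it cannot be credited to the present calculation.

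**Conclusion.** The point holds. For the planned ANOVA, and for a two-sided two-group t or rank test, 30 women per group including 10% dropout does not give 80% power for a 1-point difference with SD 1.4. At 27 evaluable per group, ANOVA power is about 76% at best and 63% with evenly spaced means, and a two-sided t-test has about 73%. The omnibus shortfall is modest under the favourable pattern. The larger loss is at the Scheffe step, with about 55% for one given contrast.

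These figures assume a common SD of 1.4, exactly 10% loss and no covariate adjustment. Multiple imputation is planned for missing outcomes, but it is not credited here with restoring the information lost through dropout.

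The finding is a mismatch between the sample size section and the analysis section, together with an unstated test and sidedness. How the figure of 30 was obtained cannot be determined from the article.

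**What to change.** Restate the Sample size estimation section without changing enrolment:

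- Name the test, its sidedness and the assumed pattern of the three means.
- State that 90 women, about 81 evaluable, give about 76% power for the planned ANOVA at a 1-point difference if one group differs from the other two (63% if the means are evenly spaced), and about 55% for one given Scheffe contrast. Alternatively, give the differences detectable at 80% power: about 1.04 points for the ANOVA under the favourable pattern and 1.27 for one Scheffe contrast.
- If the analysis is revised before the data are analysed, for example by prespecifying the 4-cm score as a covariate or choosing a less conservative pairwise procedure, recompute the power for that analysis and state the correlation assumed.

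The cost is wording only: no extra women and no change in conduct. The downside is that the stated power becomes less favourable.

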### Randomization and blinding

A person not involved in the study will use the computer-generated six-block randomization technique to determine the allocation sequence with a 1:1:1 ratio. In order to ensure allocation concealment, this person will write the type of intervention based on the predetermined sequence and put it in an opaque envelope; these will then be encoded. The questionnaires are encoded as well. Accordingly, for a participant receiving the intervention in a pocket encoded with “1”, a questionnaire with the same code will be completed. To observe blinding during data collection, one of the coworkers will perform the intervention plan and another coworker who knows nothing about the intervention will collect the data. Finally, once the questionnaires are gathered and their data are imported into SPSS-16 software, it will be determined which codes should be assigned to group A and which codes to group B or C. Afterwards, analysis of the data will be performed. The person performing the data analysis will also be blind to the type of intervention used for each group (Fig. 1).

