**Methods/design:**

In a randomized controlled trial, 90 primigravida women who attend for childbirth will be randomly assigned to one of three groups (intervention groups of either body acupressure or auricular acupressure; control, consisting of routine care). Computer-generated six-block randomization techniques will be used to determine the allocation sequence with a 1:1:1 ratio. To hide the allocation, the type of intervention will be written according to the generated sequence and put in opaque envelopes; these as well as questionnaires will be encoded. The pain score for all participants will be measured at the peak uterine contraction at 4-cm cervical dilation and at 10-cm dilation based on a visual analog scale (VAS). The duration of the active phase of labor in these groups will be recorded too. Data will be imported into SPSS-16 software. First, normality of the data distribution will be investigated. To compare labor duration among the research groups, ANOVA will be used, which will be followed, in case of significance, by the Scheffe post hoc test. Furthermore, Chi-squared test will be used to compare the categorized demographic variables and ANOVA or Kruskal–Wallis tests will be used to compare the quantitative variables in the studied groups. A significance level of 0.05 is considered significant.

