### Inclusion and exclusion criteria

#### Inclusion criteria

The inclusion criteria in the present study are primigravida women aged 19–35 years at gestational age of 37–42 weeks with a singleton pregnancy, cephalic presentation, no history of chronic diseases such as diabetes, cardiovascular disease, hypertension, hepatic and renal disorders, etc., a lack of pregnancy complications such as preeclampsia, gestational diabetes, bleeding, etc., a height above 150 cm, and admission at the beginning of the active phase (3–4 cm dilation).

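### One fixed block size of six, in a single-centre trial with visibly different arms, lets up to one allocation in five be deduced before consent: an avoidable risk of selection bias, not evidence of it

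*Protocol article*

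**What the plan says.** On the sequence, the section Randomization and blinding says: "A person not involved in the study will use the computer-generated six-block randomization technique to determine the allocation sequence with a 1:1:1 ratio". The abstract repeats the scheme and adds that "90 primigravida women who attend for childbirth will be randomly assigned to one of three groups". Neither place mentions varying block sizes or stratification.

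On concealment and masking, the same section has the outside person place the assignments in opaque, coded envelopes. One coworker delivers the intervention, another who is unaware of it collects the data, and the analyst is masked. No masking of the person who recruits is described.

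On recruitment, Informed consent process says "The first author will explain the research objectives and method to pregnant women meeting the inclusion criteria" when they are admitted to the labor and birth ward, and then "The first author will then obtain written consent from patients willing to participate in the trial".

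On the arms, Administration of intervention describes thumb pressure on body points, adhesive seeds on the ear, or routine care with no sham. The Background describes a single-centre trial.

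**The concern.** When every block has the same known size, its end can be worked out from what came before. Once five women in a 2:2:2 block have been allocated, the sixth arm is certain, and no envelope need be opened to know it. Here the features that make this practicable come together: one centre with no stratification stated, three arms that can be told apart by looking, and slow enrolment. Trial status gives August 2018 to about December 2019, some 17 months, so 90/17 is about 5 women a month and a block lasts around a month.

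If a recruiter could foresee an assignment, the decision to approach a woman, or the way the study is put to her, could depend on the arm she would get. The groups would then differ before treatment. Masking the data collector and the analyst does not repair that. The primary outcome is a self-rated pain score, and the default comparison under Data analysis is an unadjusted one-way ANOVA, so such a difference would pass into the main result.

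**Working it through.** The article gives no predictability figure to reproduce, so the check is an exact enumeration.

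**Inputs**
- Block size 6, from "computer-generated six-block randomization technique" (Randomization and blinding), read as blocks of six.
- Ratio, from "to determine the allocation sequence with a 1:1:1 ratio": 2 + 2 + 2 in each block.
- Total 90 women (abstract): 90/6 = 15 complete blocks.
- Assumption: the observer knows the block size, where each block starts, and every earlier allocation in it.

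**Certain allocations.** The number of distinct orders is 6!/(2!·2!·2!) = 90. An allocation is certain when only one arm remains in the block.
- Positions 1 to 4: never certain, since at least three slots remain and no arm can fill more than two.
- Position 5: certain when the last two slots hold the same arm. That occurs in 3 × 4!/(2!·2!) = 18 orders, and 18/90 = 0.20.
- Position 6: always certain.

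The expected number per block is 0.20 + 1 = 1.2, so the share is 1.2/6 = 20%. Over 15 blocks, 15 × 1.2 = 18 of 90. This is an average over possible lists: 15 sixth places are always known, plus on average 3 fifth places.

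**Partial knowledge.** An arm is already excluded at position 3 if the first two allocations match (1/5), and at position 4 unless the first three all differ (1 − 36/90 = 0.60). It is always excluded at positions 5 and 6. The best guess is the arm with most slots left.

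| Position | Next arm certain | An arm excluded | Best guess right |
|---|---|---|---|
| 1 | 0 | 0 | 0.333 |
| 2 | 0 | 0 | 0.400 |
| 3 | 0 | 0.20 | 0.500 |
| 4 | 0 | 0.60 | 0.533 |
| 5 | 0.20 | 1 | 0.600 |
| 6 | 1 | 1 | 1.000 |
| Mean | 0.200 | 0.467 | 0.561 |

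The best guess is thus right 56% of the time, against 33% by chance.

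**Alternative reading: six blocks of 15 (5:5:5).** The expected number of certain allocations per block is 1 + 4/14 + (4/14)(3/13) + (4/14)(3/13)(2/12) + (4/14)(3/13)(2/12)(1/11) = 1.364. The share is 1.364/15 = 9.1%, and 6 × 1.364 = 8.2, about 8 of 90.

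**Effect of varying the size.** This was simulated with 300 lists of 90, sizes equally likely, and an observer who knows the set of sizes but not their order. Sizes 3/6/9 leave 3.8% of allocations certain (0.038 × 90 = 3.4 women), and sizes 6/9/12 leave 2.4% (0.024 × 90 = 2.2 women). Best-guess accuracy falls much less, to 55% and 53%. The gain is mainly in removing certainty.

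**The case against.** The strongest reply is that the article's concealment is sound in its main parts. The list is made by someone outside the study, the envelopes are opaque and coded, and the people who intervene and who collect data are separated. The 20% needs three things the article does not establish: that the recruiter knew the block size during enrolment, knew where blocks began, and learned every earlier allocation. Printing the scheme in an article dated 23 December 2019, when data collection was expected to finish that month, does not show who knew it earlier. All of this stands. It makes 20% a ceiling, but it does not remove the fixed block.

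A reader might infer that the first author screens women and decides eligibility. Informed consent process does not say so. It has the first author speak to women who already meet the criteria and take their consent.

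A reader might also see a lever in the two eligibility lists that end in 'etc.' ("no history of chronic diseases such as diabetes, cardiovascular disease, hypertension, hepatic and renal disorders, etc" and "a lack of pregnancy complications such as preeclampsia, gestational diabetes, bleeding, etc., a height above 150 cm"). That is weak. Those lists concern chronic disease and pregnancy complications, offer little room to divert a woman for anxiety or early pain, and are the kind of detail a full protocol may complete.

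Finally, there is a partial safeguard. Pain is recorded at 4 cm in all groups, and Data analysis allows multiple linear regression for potential confounders. Steering by early pain could show as imbalance there. Selection on unmeasured features would not.

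**Conclusion.** The point holds as a conditional design weakness. A single block size of six at 1:1:1, with one centre and visibly different arms, makes up to 20% of allocations (an expected 18 of 90) knowable before consent to someone with full knowledge of the sequence so far. On the less natural reading of six blocks of 15 the ceiling is about 9%. With incomplete knowledge the share is lower.

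A reader might conclude that one allocation in five was in fact known, or that recruitment was steered. The documents support neither. They do not state who judges eligibility or whether the recruiter sees earlier allocations, and they give no basis for sizing any bias on the VAS or in minutes of labor.

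**What to change.** **If any women remain to be enrolled:** have the outside person generate the rest of the sequence in permuted blocks of randomly varying size (for example 3, 6 and 9) and keep the sizes from the trial team. The cost is one new list and a sentence in Randomization and blinding. The downside is a slight imbalance if recruitment stops inside a block; a block of nine holds three per arm, so one arm could lead another by at most three. Requiring sign-off of eligibility before an envelope is opened would not serve instead, because the prediction needs no envelope.

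**If enrolment is complete,** which Trial status makes likely:
- report the fixed block size as a limitation;
- state whether the person recruiting knew earlier allocations;
- adjust the 10-cm pain comparison for the 4-cm VAS score, which is already collected. Administration of intervention also places the first body pressure at 4 cm, so the report should say whether that score was taken before it. Only then is it a clean baseline.

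These steps need no new data beyond a statement of roles and timing. The adjustment addresses only selection that acts through early pain.
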